## **Funding**

This trial is funded by the Rebecca L Cooper Medical Research Foundation.

## **Summary of proposal in layman's terms**

Osteoarthritis is a common joint disorder for which there is no cure. Knee osteoarthritis is the most common form of osteoarthritis. Exercise is a core treatment for knee osteoarthritis. Muscle strengthening exercise has been shown to improve pain and function and is recommended by clinical guidelines. Yoga is a mind-body exercise intervention that can provide increased flexibility, muscle strength, physical balancing, improved fitness, and has demonstrated pain-relieving properties. Yoga, with its potential for improving musculoskeletal function, nervous system, and sympathetic activity, may therefore have greater benefits than commonly used strengthening exercise.

Previous studies of yoga in knee osteoarthritis patients have been of low-quality with a high risk of bias and did not perform subgroup analyses to identify patients who may specifically benefit from yoga. This randomised controlled trial aims to compare the effectiveness of the 12-week yoga program (12 weeks of yoga (3x/week)) on knee pain in knee osteoarthritis patients with a priori subgroup analysis of knee osteoarthritis patients with neuropathic pain compared to strengthening exercise. If successful, yoga can be easily implemented as a complementary treatment along with conventional treatment to improve the management of knee osteoarthritis.

**Abstract:**

Osteoarthritis (OA) is one of the major causes of pain and disability in the Australian population. Knee OA is the most common form of OA. Currently, there is no disease-modifying treatment available for knee OA.

Knee OA can be categorised by its manifestation characteristics at the structural and symptomatic levels. While biomarkers including MRI markers have enabled stratification of OA patients based on structural abnormalities, analyses of data from large observational studies and clinical trials have suggested the existence of distinct pain phenotypes (1-3) in knee OA. The pain phenotype can be defined as a subtype of OA that shares a distinct underlying pain mechanism. The pain phenotype of OA is complex and may be influenced by psychological factors (e.g. depression, pain-related fear, and anxiety) (4-6) and central pain processing (central sensitisation) (7, 8). The common discrepancies observed between the symptom severity and structural findings of knee OA may also be attributed to these factors (9). Pain is maintained by nociceptive, central, or neuropathic inputs and there is evidence of these in OA (10-12). Various studies using painDETECT have reported a 5-50% prevalence of neuropathic pain type in knee OA populations (10, 13).

Current pharmacological treatments for patients with symptomatic OA are palliative and primarily focus on pain relief. There is evidence that non-pharmacological treatments, such as exercise therapy (aerobic, muscle-strengthening, etc.) improve pain, function, depression, and quality of life (QoL) in people with OA (14). However, many studies are of low quality and had a high risk of bias, mainly due to comparing to a usual care arm (14-16). Increasing evidence demonstrates that neuropathic pain may contribute to the pain experience for a subgroup of OA patients. Therefore, it is possible that OA patients will show greater benefit from centrally-acting non-pharmacological therapies such as yoga (7, 17-20).

Yoga is a mind-body therapy, and the physical component of yoga provides exercise that is consistent with recommendations for knee OA (21, 22), while the mind component has the potential to increase psychological well-being and reduce stress (23, 24), which can influence central sensitisation. Only a few studies have evaluated the effect of yoga in patients with OA. Current guidelines for the treatment of knee OA suggest a 'conditional recommendation' for yoga as an adjunctive form of exercise, and only for short-term management. The guidelines highlighted the lack of evidence and the poor quality of the existing evidence. A systematic review of yoga intervention studies (including RCT and non-RCT) in OA reported a significant effect on pain and mobility. However, they reported a lack of data on QoL and mental health (25). Small sample sizes, shorter duration of follow-up, lack of an active comparator, and poor methodological quality of previous studies prevent definitive conclusions.

The primary aim of this 24 weeks randomised controlled trial (RCT) is to investigate the effectiveness of a 12-week group-based *yoga program* (12 weeks of yoga (3x/week)) compared to a group-based *strengthening exercise program* (3x/week) on the knee pain (assessed using VAS) in knee OA patients over 12 weeks. We hypothesise that a group-based yoga program will be superior to the group based strengthening program.

A secondary aim is to assess whether the effects are moderated by the presence of neuropathic pain such that individuals with neuropathic pain respond better to a yoga program compared to strengthening exercise program than those without neuropathic pain.

If successful, yoga can be easily implemented as a complementary treatment along with conventional treatment to improve the management of knee OA.

**Background:**

Osteoarthritis (OA) is the most common joint disorder in the world and affects over 2.2 million people in Australia, with a direct health expenditure of \$3.5 billion in 2015–16 representing 28% of overall expenditure on musculoskeletal conditions and 3% of total disease expenditure (26). Given the ageing and increasingly obese population, it is not surprising that the national joint replacement registry (AOANJRR) revealed a 128% increase in knee replacement procedures from 2003 to 2018 (27).

Despite its substantial disease burden, there is no approved disease-modifying treatment available for OA. Traditional pharmaceutical therapies, i.e. analgesics, corticosteroids, and non-steroidal anti-inflammatory drugs (NSAIDs) are, at best, only modestly effective for pain and show no effect on joint structures, with end-stage OA treated with costly joint replacements. There is evidence for non-pharmacological treatments, such as exercise (aerobic, muscle-strengthening, etc.) and physical therapy which suggests that it reduces pain, improves function, and quality of life (QoL) in OA populations; however, many studies are of low quality and high risk of bias mainly by comparing to a usual care arm (15, 16, 28).

We have shown that OA is a heterogeneous disease with multiple phenotypes that may require somewhat different approaches for each patient in order to optimise treatment. Analyses of large observational and clinical trial data have suggested the existence of distinct pain phenotypes in knee OA (1-3, 13). This pain phenotype of OA can be defined as a subtype of OA that shares a distinct underlying pain mechanism. The pain phenotype of OA is complex and may be influenced by psychological factors (e.g. depression, pain-related fear, and anxiety) (4-6) and neural sensitisation (7, 8). The occasional discrepancies observed between the symptom severity and structural findings of knee OA and the existence of persistent pain even after total knee replacement also indicates these factors (9, 29).

There is increasing clinical evidence to suggest that neuropathic pain may contribute to the pain experience in OA patients (10). Given that central sensitisation plays a role in chronic neuropathic pain, centrally-acting physical exercises may be effective (7, 13, 17). The animal models of severe OA have shown features of neuropathy and link the associated nerve damage to the progression or severity of OA (30, 31). Preliminary studies in OA patients with neuropathic pain phenotype have demonstrated that treatment with the non-standard analgesics such as tricyclic antidepressants and gabapentinoids, may be more effective than conventional treatments (13).

Yoga is a mind-body exercise constituting physical postures (*asanas*), breathing practices (*pranayama*), meditative mental focus (*dhyana*), and relaxation as the four standard components (32). With the increasing prevalence of yoga use globally, it is becoming a more popular exercise to achieve and maintain well-being and health (33-35). Yoga has been used clinically as a therapeutic intervention for improvement in pain, stiffness, swelling, and mobility symptoms in older adults and is recommended by several clinical guidelines for individuals with OA (21, 36-40). However, the current guidelines for the treatment of knee OA suggest a ‘conditional recommendation’ for yoga as an adjunctive form of exercise, and only for short-term management. The guidelines highlighted the lack of evidence and the poor quality of the existing evidence.

The mechanisms of action of yoga in OA may extend beyond the exercise component. The physical component of yoga provides exercise that is consistent with recommendations for knee OA, while the mind component of yoga has the potential to increase psychological well-being and reduce stress, improve function, and alleviate OA associated pain (41). A previous

trial has reported that sitting meditation without any physical activity component improved function in OA patients (42). A network meta-analysis assessing the effects of various non-pharmacological interventions on pain relief in patients with OA reported yoga as the most effective intervention for patients and with a high adherence rate (43). Another recent systematic review synthesizing evidence of effectiveness and safety of yoga for OA patients identified nine randomized controlled trials of low methodological quality and potential risk of bias and provided a weak recommendation to support the use of yoga in knee OA (44). Hence, given the relative scarcity of robust, high-quality conclusive evidence for yoga in OA, we aim to evaluate the effect of yoga, compared to strengthening exercise in patients with knee OA and to assess whether the effects are greater with yoga in the subgroup of patients with neuropathic pain than in those without neuropathic pain.

Comparative effectiveness research (CER) is a research methodology that reduces the translation gap between clinical research and everyday clinical practice to enable the delivery of the most cost-effective health care to the target population (45). Although CER evidence can be synthesized in the form of systematic reviews, meta-analysis, and decision modelling using the existing real-world data (RWD) [e.g. administrative claims, electronic medical records, registries and other clinical cohorts, and case-control studies], RCTs are still the most rigorous method of generating highest quality CER evidence (46). Moreover, physical therapy/exercise, of which yoga is a part, is the top priority research area for assessing the patient-centred comparative safety and effectiveness of therapies in the OA population (47). Hence, we plan to include CER components by comparing two active physical exercise programs (i.e. *yoga program* or *strengthening exercise program*) and assess the patients' reported outcome and subsequent cost-effectiveness of *yoga program* versus *strengthening exercise program* in the symptomatic knee OA population. We hypothesise that yoga will outperform strengthening exercise and we aim to demonstrate that, compared with strengthening exercise, yoga may be an effective and cost-effective therapy for managing pain and reducing the functional limitations that impact the QoL in patients with knee OA.

**Study aims and hypotheses:**

The primary aim of this 24-week RCT is to compare the effectiveness of a 12-week *yoga program* (12 weeks of group-based yoga (3x/week)) on reducing knee pain (assessed using VAS) over 12 weeks in knee OA patients compared to a 12-week group-based *strengthening exercise program* (3x/week). We hypothesise that yoga will outperform strengthening exercise and we aim to demonstrate that, compared with strengthening exercise, yoga may be an effective and cost-effective therapy for managing pain and reducing the functional limitations that impact the QoL in patients with knee OA. A secondary aim is to assess whether the presence of neuropathic pain moderates the effects of yoga compared to strengthening exercise.

**Methods:****Study design:**

Single centre comparative effectiveness RCT.

**Study participants:**

We will recruit 126 knee OA participants with knee pain from the southern Tasmania region of Australia. We will use a proven recruitment strategy, including collaboration with general practitioners, specialist rheumatologists, orthopaedic surgeons, physiotherapists, and advertising through radio, TV, newspaper, social media, community notice boards, hospital notice boards, community newsletters (e.g. Arthritis Tasmania), local press and newsletters (e.g. council newsletters such as the Glenorchy Gazette, Eastern Shore Sun, Hobart City Council equivalent), physiotherapy practice's (e.g. BodySystem, Allcare physiotherapy, Integrated Physiotherapy, etc.) and GPs and exercise physiologist practising in the region. This is the approach we have taken to successfully recruit participants for the large community-based trials across a range of musculoskeletal conditions. We will also reach out to the participants of the previous studies for knee osteoarthritis to seek their interest in participating in this trial.

**Inclusion criteria:**

1. Aged  $\geq 40$  years
2. Knee pain on most days for at least six months
3. VAS knee pain intensity of  $\geq 40$  mm in the last month.
4. Meet American College of Rheumatology (ACR) clinical criteria for the diagnosis of knee OA
5. Be willing to participate in a group yoga program or group strengthening exercise program three times per week for 12-weeks and can attend on the days/times of the week that scheduled classes are running.

**Exclusion criteria:**

1. Patients currently or in the past three months engaged in strengthening exercise or yoga program
2. Other forms of inflammatory arthritis (especially rheumatoid arthritis and gout).
3. A significant knee injury that required treatment within the last six months.
4. Arthroscopy or open surgery in the index knee in the last six months or planned in the next 6-8 months.
5. Injections of corticosteroids (last three months) or hyaluronic acid (last six months) in the index knee.
6. Pregnancy or breastfeeding.
7. Currently participating in any other drug/device/exercise clinical trial related to OA.
8. Presence of any serious medical illness or condition that may preclude a 24-week follow up.

9. Any condition that precludes safe participation in exercise (i.e. fails the safety for exercise clearance; see below for the procedure for this).
10. Unable to walk without a gait aid.
11. Inability to provide informed consent in English.
12. Plan to start exercise or another new treatment for knee OA in the next six months.
13. Planned absences (e.g. trips away) of >2 weeks maximum during the 12-week period.

### **Screening:**

Volunteers will be telephone screened for general eligibility and invited to Menzies for a screening visit which comprises of symptom assessments, medication history questionnaires, safety for exercise clearance, and clinical assessment for ACR criteria. In the case of bilateral eligible knees, the most symptomatic knee will be the study knee. In the case of bilaterally eligible knees with equal symptoms, the dominant knee will be studied.

### **Safety for exercise clearance:**

During the screening, the Adult Pre-exercise Screening Tool (stage 1) will be administered. The tool was developed by Exercise and Sports Science Australia (ESSA), Fitness Australia and the Sports Medicine Australia (SMA) to identify those individuals with a known disease, or signs or symptoms of a disease, who may be at a higher risk of an adverse event during physical activity/exercise. There are seven items listed on the questionnaire. Individuals who answer yes to any of the seven questions will be referred to their GP for safety for exercise clearance before they can be enrolled in our study.

This approach of screening patients for exercise participation is in line with the recommendation from the American College of Sports Medicine. In particular, it will help identify individuals at risk of exercise-related sudden cardiac death and/or acute myocardial infarction while also avoiding excessive physician referrals which create barriers to exercise participation.

### **Randomisation and blinding:**

Allocation of participants in a 1:1 ratio to either a 12-week *yoga program* or *strengthening exercise program* will be based on computer-generated random numbers prepared by a statistician with no involvement in the trial. Code-break for the full randomisation schedule will be maintained by the administering institute.

The assessors will be blinded to treatment allocation for objective outcome measures. Allocation concealment and blinding will be ensured by having two research nurses coordinate the trial. Assessments will be taken by the research nurse blinded to the group allocation.

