**Primary outcome:**

Change in knee pain assessed by VAS for over 12 weeks. Pain will be evaluated at each time point using a 100mm VAS and asked: “On this line, how would you rate your overall average knee pain in the last one week”? For knee pain assessed using VAS, terminal descriptors will be 0mm = no pain, 100mm = worst pain possible.

**Secondary outcomes:** (overall change from baseline to week 12 and overall change from baseline to week 24 are separate outcomes)

1. Change in VAS knee pain over 12 weeks in patients with painDETECT>12
2. Change in VAS knee pain over 24 weeks.
3. Change in WOMAC knee pain, WOMAC stiffness, and WOMAC knee function over 12 weeks and over 24 weeks.
4. Change in physical function as assessed by 30s Chair Stand Test, 40m Fast Walk Test and Stair Climb Test over 12 and over 24 weeks
5. OMERACT\_OARSI responders (meeting responder criteria) at week 12, and 24 weeks
6. Change in biomarker (urinary CTX-II, serum COMP, and serum hyaluronan) and systemic inflammatory markers (hs-CRP, IL-6, TNF- $\alpha$ ) over 12, and over 24 weeks
7. Change in Patient Health Questionnaire (PHQ-9) scales over 12, and over 24 weeks
8. Change in patient global satisfaction score over 12, and over 24 weeks
9. Change in painDETECT scores over 12, and over 24 weeks
10. Change in leg muscle strength (quadriceps) over 12, and over 24 weeks
11. Change in gait speed from baseline to week 12 and baseline to 24 weeks

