***Sample Size calculation:***

Our power calculations are based on a sample size that can document the minimal clinically important difference (MCID) in VAS knee pain superior to yoga compared to strengthening exercise. Based on the MCID of 15mm in VAS pain [a numerical scale ranging from 0 (no problem) to 100 (maximum problem)], two-sided significance level of 0.05, 90% power and SD of VAS pain change 22.5, we will need a total of 98 participants. Assuming a worse scenario of 20% dropout, we will need 126 participants.

The above sample size will allow us to detect a non-inferiority of yoga with strengthening exercise. Non-inferiority would be declared if the mean change in knee pain (assessed using VAS) in the yoga group was not significantly worse than the mean change in the strengthening exercise group, within a pre-stated margin of non-inferiority ( $\Delta$ ), in this case, set at 10 mm. Overall, 126 participants will give us 80% power to detect the non-inferiority of yoga compared with strengthening exercise.

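### No stratification or blocking is described and painDETECT is not in the primary model, although neuropathic pain is the planned moderator; balancing on it would be a cheap but modest gain

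*Combined protocol and SAP*

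**What the plan says.** - **Aim.** Under Study aims and hypotheses: "A secondary aim is to assess whether the presence of neuropathic pain moderates the effects of yoga compared to strengthening exercise". The lay summary also presents the neuropathic-pain subgroup as planned in advance.
- **Outcome.** The protocol's secondary outcomes include "Change in VAS knee pain over 12 weeks in patients with painDETECT>12". The SAP repeats it, third in its list.
- **Expected frequency.** The Abstract reports: "Various studies using painDETECT have reported a 5-50% prevalence of neuropathic pain type in knee OA populations". It does not give the cut-off behind that range. No eligibility criterion enriches for neuropathic pain.
- **Allocation.** Randomisation and blinding gives a 1:1 ratio that "will be based on computer-generated random numbers prepared by a statistician with no involvement in the trial". No stratification factor and no blocking are mentioned there or elsewhere.
- **Primary model.** Statistical Analyses (protocol) and Data analysis (SAP) name treatment, time and the baseline value of the outcome. They add possible adjustment or interaction for age, sex, BMI, disease severity, comorbidities, health status and pain medication. The model used for the final manuscript has the baseline value, age, sex and BMI. painDETECT is in none of these lists. It enters only a separate moderation analysis, which the SAP labels exploratory.
- **Timing.** The assessment schedule places both painDETECT and randomisation at baseline, without stating their order.

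**The concern.** The trial expects neuropathic status to change the response to yoga and measures it at the visit where people are randomised. Yet status is used neither in the described allocation nor in the primary model. Two things are then left to chance.

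1. The subgroup may be small and unevenly split between arms, which costs precision in the subgroup comparison and the interaction.
2. The arms may differ in the share of participants with neuropathic pain. If status also predicts pain change beyond baseline VAS, the realised primary estimate shifts somewhat.

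Both could be limited with a measurement the trial already takes.

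**Working it through.** **Inputs.** From Sample Size calculation: "two-sided significance level of 0.05, 90% power and SD of VAS pain change 22.5", an MCID of 15 mm, "we will need a total of 98 participants", and "Assuming a worse scenario of 20% dropout, we will need 126 participants". From the Abstract: prevalence 5-50%. Assumptions: the prevalence range applies to painDETECT above 12, and SD 22.5 mm and a 15 mm effect also apply within the subgroup and to the interaction.

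**The plan's own figure.** A two-sample t-test with 49 per arm has 90.4% power, so 98 is reproduced. With 20% dropout, 98/0.8 = 122.5, or 123; the stated 126 is within 3% of that.

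**Subgroup size.** n = 126 × prevalence: 6.3 at 5%, 12.6 at 10%, 25.2 at 20%, 37.8 at 30% and 63 at 50%. After 20% dropout the range is about 5 to 50.

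**Split within the subgroup.** Under simple randomisation the number in one arm is k ~ Binomial(n, 0.5). A split is 2:1 or worse when the smaller arm holds n/3 or fewer. For n = 6 only k = 3 escapes, so the probability is 1 − 20/64 = 0.69. With arms fixed at 63 each, k is hypergeometric.

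**Cost of an uneven split.** Information relative to an even split is 4k(n−k)/n². At 1:2 this is 4 × (1/3) × (2/3) = 0.89, an 11% loss. Under simple randomisation the mean of k(n−k) is n(n−1)/4, so expected relative information is (n−1)/n and the average loss is 1/n.

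**Subgroup power for 15 mm.** Two-sample t-test with all 126 evaluable, averaged over chance splits, against a near-even split.

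| Prevalence | n | 2:1 or worse, simple | 2:1 or worse, 63/63 arms | Average loss 1/n | Power, simple | Power, balanced |
|---|---|---|---|---|---|---|
| 5% | 6 | 69% | 68% | 17% | 8.8% | 9.8% |
| 10% | 13 | 27% | 24% | 8% | 18.4% | 19.5% |
| 20% | 25 | 11% | 7% | 4% | 34.7% | 35.8% |
| 30% | 38 | 3.4% | 1.1% | 3% | 50.5% | 51.6% |
| 50% | 63 | 1.1% | <0.1% | 1.6% | 73.3% | 74.0% |

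With 6 people the chance that all fall in one arm is 2 × 0.5⁶ = 3.1%.

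**Arm difference in neuropathic share.** With 63 per arm, a gap of 10 points or more means |2k − n| ≥ 6.3. The hypergeometric probabilities are 0% for n = 6, 8% for 13, 18% for 25, 17% for 38 and 29% for 63. If arm sizes are not fixed, they are 16%, 23% and 25% for 25, 38 and 63.

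**Effect of such a gap on the primary estimate.** If neuropathic status shifts VAS change by 5 to 15 mm (an assumption; the documents give no figure), a 10-point gap moves the estimate by 0.10 × 5 = 0.5 mm to 0.10 × 15 = 1.5 mm. The standard error is 22.5 × √(2/63) = 4.0 mm.

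**What balancing cannot cure.** With balanced arms, the interaction's standard error is 22.5 × √(4/n + 4/(126−n)). The difference in effect detectable with 80% power is 2.80 times that: about 51 mm at 5% prevalence and 22 mm at 50%. Both exceed the 15 mm MCID.

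**The case against.** The case against has real force.

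- **Little power is bought.** Balancing adds about 1 point at every prevalence. Where a bad split is likely, power is poor whatever the split. This stands: the larger weakness is subgroup size and the absence of any stated interaction power.
- **The two risks do not peak together.** A lopsided subgroup belongs to low prevalence; a 10-point arm difference belongs to 20% and above. This stands, and rules out the reading that the subgroup is liable to be badly split across the whole 5-50% range.
- **Confounding.** A reader might infer that an arm difference confounds the primary comparison. It does not. Randomisation makes it chance imbalance, which the confidence interval covers, and a moderator need not be prognostic. At most, one realised estimate is shifted slightly, and adjustment would recover some precision.
- **Other candidate modifiers.** The PHQ-9 section says depression may modify the effect, and the analysis sections foresee treatment interactions with several covariates. So painDETECT is not the only factor the plan names. It is the one that carries a stated aim and its own outcome.
- **Exploratory status.** The SAP tests moderation by an interaction using all participants and calls it exploratory. The secondary aim therefore does not rest on the within-subgroup comparison alone.
- **Silence.** One might conclude that allocation was unstratified. The documents only fail to describe stratification or blocking.

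What survives is narrower: the planned moderator is collected at the randomisation visit and used in neither the described allocation nor the primary model, and using it would need no new measurement.

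**Conclusion.** The point holds as a low-cost improvement, not as a threat to the primary result. On the plan's figures, a split of 2:1 or worse is a serious prospect only when the subgroup numbers about 6 to 13 (69% to 27%). It is uncommon at 25 (11%) and negligible at 63 (1%). At 20-50% prevalence a 10-point arm difference in neuropathic share has a 17-29% chance with equal arms. The return from balancing is small, and it leaves the moderation aim with low power.

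The size rests on applying the Abstract's prevalence range to the above-12 cut-off, on the planning SD holding within the subgroup, and on the undescribed method being simple or equal-arm randomisation. If the list was in fact stratified on painDETECT, only the reporting and the model covariate remain at issue.

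**What to change.** **Design text.** Under Randomisation and blinding, specify permuted blocks of varying size, stratified by baseline painDETECT (above 12 versus 12 or less). Require the questionnaire to be scored before the allocation is released.

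**Analysis text.** Under Statistical Analyses and the SAP's Data analysis, add baseline painDETECT status as a covariate in the primary mixed model.

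**For this trial.** The SAP already describes the final analysis, so the list cannot be changed. State whether allocation was blocked or stratified, report painDETECT above-12 counts by arm, and fit the primary model with painDETECT status added, at least as a sensitivity analysis. Reporting the detectable interaction beside the moderation result would show readers how little it can exclude.

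**Cost.** One further allocation list, one sequencing rule at the baseline visit and one model term, with no new measurement. The downside is that painDETECT must be complete before anyone can be allocated.
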